  2. Treatment discontinuation > 4 weeks during the medication due to adverse drug reaction or other reasons (e.g. the treatment has to be discontinued due to occurrence of other disease, migration to other places and loss to follow-up); or within 24 weeks, the accumulated duration of drug discontinuation has exceeded 8 weeks;
  3. Subjects who withdraw the drug by themselves and give up continuing the trial;
  4. Due to serious adverse drug reaction, the drug must be withdrawn in advance.
  5. Those with poor compliance and failing to take the drug according to the schedule or design;
  6. Those with concurrent occurrence of other serious diseases and the investigator considers inappropriate to continue the medication;
  7. Those failing to complete all the examination items as required and thus not evaluable.

5.5 Trial assessments:

The screening visit will be completed within 3 weeks (21 days) before the first administration of the investigational drug. The baseline visit and randomization will be conducted on the day of the first administration, and informal visits will be conducted every 4 weeks to understand the medication and adverse events of the subjects. Formal visits will be conducted every 12 weeks, and the visit results will be recorded. The endpoint visits will be conducted at week 52. In addition to the baseline, the time window for each visit is ±7 days (based on the baseline).

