**7. Efficacy evaluation:**

7.1 Primary endpoints:

Improvement in Sharp score of X-ray of affected joints.

7.2 Secondary endpoints:

1. Proportion of subjects reaching ACR20, ACR50 and ACR70: ACR50 and ACR70 are defined as 50% and 70% improvement respectively using the same criteria as ACR20.
2. Average changes of ACR core parameters relative to the baseline level
3. Average change of HAQ score from baseline to Week 52
4. Time for each treatment group to reach ACR20, 50 and 70
5. The proportion of subjects with low disease activity at each visit
6. The proportion of subjects achieving disease remission at each visit
7. MRI changes (joint space narrowing and bone erosion)

7.2.1 The response definition of ACR20 is: there is 20% improvement in the number of swollen and tender joints (28), as well as 20 % improvement in at least 3 of the 5 following items:

1. The VAS score of pain assessed by the subject;
2. The VAS score of overall disease condition assessed by the subject;
3. The VAS score of overall disease condition assessed by investigator;
4. Health Assessment Questionnaire (HAQ);
5. Acute phase reactant (ESR or CRP).

7.2.2 DAS28:

[figure not shown]
(28 joints)

The disease activity score of 28 joints will be calculated as follows:

DAS28 = 0.56 × + 0.28 × + 0.7 × ln(ESR) + 0.014 × GH

TJC: Tender joint count, SJC: Swollen joint count, ESR: erythrocyte sedimentation rate (in mm/h), GH: general health status expressed in the 100 mm VAS.

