**9. Statistical methods:**

9.1 Selection of statistical analysis data:

Intent-to-treat (ITT): all subjects eligible and enrolled after screening and having taken at least one dose of the drug and received at least one post-treatment effectiveness evaluation; LOCF (last observation carry-forward) will be adopted for those subject’s data not observed during the whole treatment course, that is, estimating the missing values of important indicators using the closest observed data. The ITT analysis will be used in this trial.

Safety population: it includes all subjects having taken at least one dose of the drug and received at least one post-treatment safety evaluation.

9.2 Statistics Analysis Plan:

Statistical analysis will be carried out using the SAS statistical analysis software. A sample size of 90 patients was estimated for the open label period with the assumption that mean mTSS CRF was -0.5±1.0 in the MTX plus rhTNFR:Fc group, and 2.5±5.0 in the MTX group at week 52. A sample size of 25 patients per treatment group was calculated to be necessary for more than 80% power to reject the null hypothesis of no difference among the treatment groups with an α of 0•05. Assuming loss of patients, the study required a minimum of 30 patients in each group. Two-sided test will be used for all statistical tests, and the difference tested will be considered as statistically significant if the P value is equal to or less than 0.05. Measurement data will be statistically described using mean±SD (standard deviation). Paired t-test will be used for intra-group differences before and after the treatment. Enumeration data will be statistically described using frequency (constituent ratio).

Dropout analysis: Calculate the dropout rates and the rates of dropout due to AE.

Efficacy analysis: The paired t test or nonparametric test or chi-square test will be used to evaluate the efficacy indexes.

Safety analysis: Calculate the incidence rate of adverse events and tabulate the AEs occurring during the trial, normal/abnormal changes in laboratory findings before and after the trial, as well as relationships of abnormal changes with the investigational drug

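### Section 9.1 does not exempt responder endpoints from carry-forward, so early responders later withdrawn count as Week 52 responders; its gloss also lets a later visit fill an earlier one

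*Protocol*

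**What the plan says.** Protocol section 9.1 gives a single rule for missing efficacy data: "LOCF (last observation carry-forward) will be adopted for those subject’s data not observed during the whole treatment course". It then explains that rule as "estimating the missing values of important indicators using the closest observed data". The indicators are not named, reasons for missingness are not distinguished, and nothing is said about binary endpoints. The same section adds "The ITT analysis will be used in this trial". That set requires at least one dose and at least one effectiveness evaluation after treatment.

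Section 7.2 lists three kinds of binary secondary endpoint: "Proportion of subjects reaching ACR20, ACR50 and ACR70", "The proportion of subjects with low disease activity at each visit" and "The proportion of subjects achieving disease remission at each visit". It also lists time to ACR response. The Efficacy Evaluation part of the Summary compares ACR response within and between groups at Weeks 24 and 52.

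Section 5.4 lists the categories of patients who may withdraw. They include more than 4 weeks off drug because of an adverse reaction or another reason, stopping by the patient's own choice, and "Due to serious adverse drug reaction, the drug must be withdrawn in advance". The flow chart in Attachment I has efficacy visits at Weeks 12, 24, 36 and 52 and no early-withdrawal visit.

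**The concern.** A responder endpoint at Week 52 is normally read as a response that the patient still has at Week 52. Take a patient in remission at Week 24 who is withdrawn for a serious reaction at Week 26. If the rule in 9.1 is followed as written, the Week 24 status fills Weeks 36 and 52. The regimen is credited with an outcome that the patient could not keep on it. Clinical efficacy is one of the two parts of the trial objective, so this affects a comparison that will be reported, although the primary endpoint is the Sharp score.

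A second, smaller problem is that the rule and its explanation do not describe the same operation. *Last observation* looks only backwards. *Closest observed* can look forwards, so a response could be dated to a visit before it was seen. That bears on the Week 24 comparison, the proportions at each visit and time to ACR response.

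**Working it through.** **Inputs.** From section 9.2: means of -0.5 (SD 1.0) and 2.5 (SD 5.0), two-sided alpha 0.05, 25 per group for more than 80% power, 30 per group after loss. From section 5.5 and Attachment I: baseline, then Weeks 12, 24, 36 and 52, each ±7 days. The protocol does not give response rates, dropout by arm, or response status of leavers; these are assumed below.

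**Step 1: the plan's own figure.** The difference is 3.0 and the SD is √((1² + 5²)/2) = 3.606. The normal approximation gives n = 2 × (1.960 + 0.842)² × 13/9 ≈ 22.7, so 23 per group. A pooled t-test needs 24. Welch's test needs 25 (power 80.8% at 25, 79.1% at 24). The stated 25 reproduces. Going from 25 to 30 allows for 5/30 = 16.7% loss. This step serves only to supply the number of losses.

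**Step 2: Week 52 responder rate under two rules.** Let L be the leavers in an arm of N = 30, and q the share of them who were responders when last seen. Carry-forward counts L × q of them as responders; non-responder imputation counts none. The rate therefore differs by L × q / 30.

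- Bounds for one arm with L = 5: q = 0 gives 0 points; q = 1 gives 5/30 = 16.7 points.
- Illustration: q of 50-70% on combination and 20-30% on MTX, equal losses in both arms, all combinations crossed:

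| Losses per arm | Added to combination | Added to MTX | Widening of the difference |
| --- | --- | --- | --- |
| 5 | 8.3 to 11.7 | 3.3 to 5.0 | 5 × (0.5 - 0.3)/30 = 3.3 to 5 × (0.7 - 0.2)/30 = 8.3 |
| 3 | 5.0 to 7.0 | 2.0 to 3.0 | 3 × (0.5 - 0.3)/30 = 2.0 to 3 × (0.7 - 0.2)/30 = 5.0 |

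- Reversal: with 2 combination leavers at 50% and 5 MTX leavers at 30%, the additions are 2 × 0.5/30 = 3.3 and 5 × 0.3/30 = 5.0 points. Carry-forward then narrows the difference by 1.7 points.

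The denominator of 30 assumes that every leaver had at least one effectiveness evaluation. Those without one fall outside the 9.1 analysis set and are neither carried nor counted.

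**Step 3: *last* against *closest*.** Every pattern of missed visits on the schedule 0/12/24/36/52 gives 32 cases of a visit to be filled.

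- Week 52: the two wordings pick the same visit in every case, since nothing comes later.
- Intermediate visits at nominal weeks: *closest* picks a later visit outright in 4 of 32 cases (for example, with Weeks 24 and 36 both missed, Week 36 takes Week 52 and not Week 12). It ties in 6 of 32.
- The visit window breaks the ties. A missed Week 12 (day 84) is 84 days from baseline, while a Week 24 visit in its window is 77 to 91 days away. A missed Week 24 is 77 to 91 days from either Week 12 or Week 36. A few days of scheduling then decide which value is used.
- X-ray schedule 0/24/52: no difference at nominal weeks.

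**The case against.** The best case on the other side has several parts.

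- *Reach.* Section 9.1 speaks of important indicators and names none, nor does it say whether responder status or its components are carried. A reader might infer that the protocol expressly applies carry-forward to ACR response, low disease activity and remission. It does not; the supportable statement is that they are not exempted. If they lie outside the rule, the protocol fixes no rule for them, and the same edit cures that.
- *Wording.* The second phrase is a loose explanation of a rule already named ("LOCF (last observation carry-forward) will be adopted"). A reader might blame it for the Week 52 problem. Step 3 rules that out, so it is a clarification for intermediate visits only.
- *Direction.* A reader might conclude that the Week 52 difference is biased towards the combination. Section 1 does say that etanercept acted faster than MTX in studies abroad, which makes responders among combination leavers plausible. But no dropout or response rates by arm are given, and in an open-label trial MTX patients may leave more often. The sign is not established.
- *Benchmark.* Non-responder imputation is not the truth either. Suppose completers respond at 60% and 40%, with 5 leavers per arm of whom 60% and 30% were responders. Carry-forward gives (15 + 3)/30 - (10 + 1.5)/30 = 21.7 points, non-responder imputation gives 15/30 - 10/30 = 16.7, and completers alone give 20.0. Most of that 5-point gap comes from non-responder imputation shrinking the contrast. The figures above therefore measure sensitivity to the rule, not proven inflation.
- *Group B.* A reader might think that deleting the closest-value wording stops values crossing Group B's change of regimen. Ordinary carry-forward crosses it too.
- *Mitigation.* Section 9.2 reports dropout due to adverse events, and section 8.5 continues observation after drug is stopped for some reactions, so stopping drug does not always mean missing data. Both help, but neither changes how a withdrawn patient is counted.

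What stands against the objection is that 9.1 fixes one rule, without exception, and its plain consequence for withdrawn responders is unsuitable.

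**Conclusion.** The point holds in this form. Section 9.1 sets carry-forward as the only missing-data rule and does not exempt the binary endpoints. A patient who responds early and is then withdrawn for toxicity, long interruption or giving up is, on a plain reading, a Week 52 responder. Separately, the closest-value wording allows a later visit to fill a missed Week 12, 24 or 36, and never affects Week 52.

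Neither size nor direction is fixed by the document. The loss of 5 in 30 comes from the plan's own allowance and bounds the effect on one arm at 0 to 16.7 points. The range of 3.3 to 8.3 points for the difference (2 to 5 with 3 losses) rests on assumed responder shares among leavers and equal losses. These are secondary endpoints, so the change is advisable and does not bear on the primary analysis.

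**What to change.** In section 9.1:

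1. State that for ACR20/50/70, low disease activity and remission, a patient who has withdrawn from treatment or from the trial counts as a non-responder at all later visits. Show carry-forward as a sensitivity analysis. Say that Group B's planned change of regimen is not a withdrawal.
2. Replace the closest-value wording with the last preceding post-baseline observed value, so that no later value fills an earlier visit, and name the important indicators.
3. Give one rule for an isolated missed visit in a patient who continues, including a missed Week 12, which has no earlier post-baseline value. Such a visit should not become a non-response by default: a patient who responds at Weeks 12 and 36 and misses only Week 24 is not a treatment failure.

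The cost is a few sentences and one extra sensitivity analysis. Reported response rates will be lower, by up to about 8 to 12 points in the combination arm with 5 losses and the shares assumed above, and this should be accepted openly.

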**Efficacy Evaluation:**

ACR20\50\70, DAS28, CDAI and SDAI will be compared within and between the groups at week 24 and 52 week after treatment, and Sharp score changes will be compared.

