**2. Trial objective:**

Compare the clinical efficacy and the influence on the joint radiology progression between different treatment groups of RhTNFR:Fc combined with MTX and between these groups and the MTX monotherapy.

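### The power of more than 80% belongs to one two-group contrast but is claimed for all three groups, and three unranked contrasts are each tested at 0.05

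*Protocol*

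**What the plan says.** The objective (Protocol, Section 2, repeated in the Summary) is to compare efficacy and radiographic progression "between different treatment groups of RhTNFR:Fc combined with MTX and between these groups and the MTX monotherapy". With Groups A (combination throughout), B (MTX first, combination later) and C (MTX), that is A versus B, A versus C and B versus C, with no ranking.

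Section 7.1 gives the primary endpoint as improvement in the X-ray Sharp score. It names no pair of groups and no week.

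Section 9.2 sizes the trial on these inputs: "mean mTSS CRF was -0.5±1.0 in the MTX plus rhTNFR:Fc group, and 2.5±5.0 in the MTX group at week 52". On size it says "A sample size of 25 patients per treatment group was calculated to be necessary", and 30 per group are planned to allow for loss of patients. The stated aim of that size, at α 0.05, is "more than 80% power to reject the null hypothesis of no difference among the treatment groups". All tests are two-sided, and a difference "will be considered as statistically significant if the P value is equal to or less than 0.05". The section gives no order of testing, no adjustment and no overall test acting as a gate.

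The Summary, under Efficacy Evaluation, says that the clinical indices "will be compared within and between the groups at week 24 and 52 week after treatment". A following clause adds that Sharp score changes will be compared, without naming a week.

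**The concern.** Two things do not fit together.

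- **Power.** The claim is made against a null hypothesis covering all the treatment groups, in a trial that has three. The inputs describe two. Group B has no assumed mean or SD, so the protocol holds no calculation from which three-group power, or power for any contrast with B, could follow.
- **Error rate.** Three contrasts on the primary endpoint share one unadjusted 0.05 rule, and none is designated as the one that decides the trial. In an open-label study, a significant result on any pair could be presented as the primary result. A non-significant A versus B could be read as showing that a delayed start does no harm, although the trial was not sized for that question.

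**Working it through.** **Inputs from Section 9.2:** means −0.5 and 2.5, SDs 1.0 and 5.0, two-sided α 0.05, 25 per group (30 with the allowance for loss). All Group B values below are my assumptions, because the Protocol gives none.

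**1. Reproducing the plan's figure.** Unequal-variance (Welch) t test, combination versus MTX:

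- difference = 2.5 − (−0.5) = 3.0
- standard error = √((1.0² + 5.0²)/25) = √1.04 = 1.020
- noncentrality = 3.0/1.020 = 2.94
- df = 24 × (1 + 25)²/(1² + 25²) = 24 × 676/626 = 25.9
- critical t = 2.056, power = 80.8%

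At 24 per group power is 79.1%, so 25 is exactly the size that this test requires. The pooled t test gives 82.2% at 25. At 30 per group Welch gives 87.7%. The plan's 25 is therefore a correct two-group calculation.

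**2. The three-group null and the contrasts with B.** The F test is simulated with SD 1.0 in A, 5.0 in C and the stated SD in B. The pairwise powers are Welch at two-sided 0.05.

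| Assumed B (mean ± SD) | F test, n=25 | F test, n=30 | A vs B, n=25 | B vs C, n=25 |
|---|---|---|---|---|
| −0.5 ± 1.0 (same as A) | 88% | 92% | no difference | as A vs C |
| 2.5 ± 5.0 (same as C) | 82% | 90% | as A vs C | no difference |
| 0.25 ± 2.0 | 80% | 86% | 37% | 53% |
| 1.0 ± 1.0 | 83% | 90% | above 99% | 29% |
| 1.0 ± 2.0 | 81% | 88% | 90% | 27% |
| 1.0 ± 3.0 | 77% | 85% | 63% | 24% |
| 1.0 ± 3.6 | 73% | 82% | 49% | 22% |
| 1.0 ± 5.0 | 63% | 73% | 29% | 18% |

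The mean 1.0 is midway between A and C: (−0.5 + 2.5)/2. The SD 3.6 is √((1 + 25)/2).

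**3. Familywise error.** With no true differences and equal variances at 25 per group, three pairwise t tests at 0.05 give at least one rejection in about 12% of simulated trials. Independent tests would give 1 − 0.95³ = 14.3%; the pairs share groups, so the true figure is lower. If Week 24 Sharp comparisons counted as primary too, six tests would give about 17% to 22% for a between-visit correlation of 0.9 down to 0.5.

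**4. Cost of splitting α instead.** At 0.05/3 = 0.0167, A versus C has 65.0% power at 25 and 75.2% at 30; 80% needs 33 evaluable per group. With the implied loss of 5/30 = 16.7%, that is 33/(25/30) = 39.6, so 40 randomised per group.

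**The case against.** Several counter-arguments have force.

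- **The arithmetic is right.** A reader might infer that 25 per group is a miscalculation or that true power is below 80%. The document does not support that. The figure reproduces for the two-group test, and the F test passes 80% at 25 per group if B resembles A or C, or lies midway with a small SD. At 30 per group, most of the assumed cases exceed 80%. What stands is that no stated assumption supports the three-group claim.
- **Week 52 is well signalled.** The sample-size sentence, the treatment period and the endpoint visit all point to it. The two weeks in the Summary attach to the clinical indices, not clearly to the Sharp score. The 17% to 22% error rate is therefore a conditional figure and should not be presented as what the plan prescribes.
- **An overall test could act as a gate.** If a three-group test had to be significant first, familywise error for three groups would stay at about 5%. The Protocol states no such gate.
- **Power for A versus B could be high.** It reaches 90% if B is 1.0 ± 2.0. It would be wrong to call this contrast definitely underpowered, or to call it the only question Group B answers, since B versus C is also in the objective.
- **A separate analysis plan may set an order.** It may, but the blanket 0.05 rule and the power sentence are explicit here, and such a plan would have to override them.

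**Conclusion.** The point holds in limited form. The claim of more than 80% power is valid for combination versus MTX at Week 52, naturally A versus C, and for nothing else that the Protocol specifies. For the three-group null it cannot be verified: about 63% to 88% at 25 per group over the Group B values tried. For A versus B it is about 29% to 90% with B's SD between 2.0 and 5.0. For B versus C it is about 18% to 24% with B midway and an SD of 3.0 to 5.0, and somewhat higher in more favourable cases. These ranges rest on assumed Group B values.

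The error-rate part does not depend on Group B's alternative. Three ungated contrasts at 0.05 give about 12% familywise error on the primary endpoint, roughly two and a half times nominal.

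**What to change.** In Sections 7.1 and 9.2, state:

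- The single primary hypothesis is A versus C, change in Sharp score from baseline to Week 52, at two-sided 0.05.
- If it is significant, the other two contrasts at Week 52 are tested at 0.05 in a pre-stated fixed sequence, for example B versus C and then A versus B. The order is for the sponsor to choose, before the data are seen.
- Week 24 comparisons are supportive.
- Power exceeds 80% for A versus C with 25 evaluable patients per group. No power is claimed for contrasts involving Group B.

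This costs wording only and no patients. The price is a narrower power claim, and later contrasts become descriptive if an earlier one fails. If the sponsor wants all three contrasts to carry equal weight, α must be split and the size recalculated with a stated Group B assumption. On the stated A versus C effect alone, that already means 33 evaluable per group.

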**5. Test method and course of treatment**

5.1 Test method:

The trial is a randomized, controlled, open-label, multicenter clinical study. Qualified subjects after screening will be randomly divided into 3 groups (Groups A, B and C) using centre-stratified block-permuted randomization, with 30 patients in each group and 90 patients in total:

5.2 Drug usage:

1. In MTX therapy, the initial dose is 10mg/ week, which will gradually be increased to 15 mg/ week (in Week 4);
2. At the same time, 25mg of RhTNFR:Fc (trade name: Yisaipu) will be injected subcutaneously each time, twice a week for treatment.
3. The subjects will be treated with the combined use of MTX according to the above regimen until Week 52, and endpoint evaluation will be conducted. The dose of MTX could be reduced for safety reasons. If the subjects could not tolerate the dose reduction, the event could be recorded as an adverse event. After reduction, the dose could be restored to the prescribed dosage when the investigator thinks it is appropriate.
4. Diagram of drug usage:

Group A:

(RhTNFR:Fc + MTX group), 52 weeks; n=30

Group B:

"MTX monotherapy"; n=30

(RhTNFR:Fc + MTX group)

Group C:

"MTX monotherapy"; n=30

Baseline

52 weeks

24 weeks

4 weeks

12 weeks

36 weeks

MTX dose increase stage: MTX will be increased from 10 mg/ week to 15 mg/ week

Note: Folic acid at 5 mg/ week will be given on the Day 2 of MTX administration in the trial.

5.3 Criteria for drug withdrawal:

If one of the following conditions occurs, the investigator may consider drug discontinuation for observation:

1. A serious adverse event occurs, and it has certain relationship with the investigational drug;
2. An adverse drug reaction occurs, and effective remission cannot be achieved after symptomatic treatment;
3. Laboratory tests: transaminase > 3 times the normal value or WBC < 3×109 /L, or PLT < 100×109 /L;
4. The subject has other diseases, and the investigational drug may aggravate the condition.

5.4 Withdrawal from the trial:

For the patients who withdraw during the trial, the investigator must record the reason and date of withdrawal in detail. Patients who may withdraw during the trial can be divided into the following categories:

- 1. Patients found to fail to meet the inclusion/exclusion criteria during the trial;

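### Section 9.2 names a within-group test, the paired t test, as its only parametric efficacy test and fixes no between-group test for the continuous primary endpoint, although the objective and the sample size are between-group.

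*Protocol*

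**What the plan says.** The protocol's section 2 sets the aim as a comparison "between different treatment groups of RhTNFR:Fc combined with MTX and between these groups and the MTX monotherapy". The Summary, under Efficacy Evaluation, says that the clinical indices will be "compared within and between the groups at week 24 and 52 week after treatment" and that changes in Sharp score will be compared too. The primary endpoint in section 7.1 is "Improvement in Sharp score of X-ray of affected joints", a continuous measure.

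Section 9.2 plans the sample size for a null hypothesis of equality across the treatment groups. It assumes that "mean mTSS CRF was -0.5±1.0 in the MTX plus rhTNFR:Fc group, and 2.5±5.0 in the MTX group at week 52", and continues: "A sample size of 25 patients per treatment group was calculated to be necessary for more than 80% power".

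On tests, section 9.2 first says: "Paired t-test will be used for intra-group differences before and after the treatment". A few sentences later, under efficacy analysis, it says: "The paired t test or nonparametric test or chi-square test will be used to evaluate the efficacy indexes". No two-sample t test, analysis of variance or analysis of covariance is named anywhere in the protocol.

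**The concern.** The protocol defines the paired t test as a before-and-after test inside a group and then lists it as the parametric test of efficacy. A paired test of Sharp score in one arm asks whether that arm changed from baseline. It does not ask whether two randomised arms differ, which is the question in the objective and in the powered null.

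For the primary endpoint the other two options do not settle the matter. Chi-square is for proportions. An unidentified nonparametric test could be a signed-rank test (within-group) or a rank-sum test (between-group), and the word "or" leaves the selection open in an open-label trial.

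At stake is the main conclusion. If the arms were judged by whether each changed significantly from its own baseline, the benefit of randomisation would be lost and the stated 5% level would not apply to the treatment comparison.

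**Working it through.** **Inputs (section 9.2).** Mean change −0.5, SD 1.0 (combination); mean change 2.5, SD 5.0 (MTX); 25 per group, raised to 30 for losses; two-sided 0.05; power above 80%. I read the pair as 52-week combination against MTX alone (Group A against Group C).

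**1. Reproduce the stated sample size as a between-group comparison.**
- Difference: 2.5 − (−0.5) = 3.0.
- Root-mean-square SD: √((1.0² + 5.0²)/2) = √13 = 3.606.
- Normal approximation: n = 2 × [3.606 × (1.960 + 0.842)/3.0]² = 22.7, so 23 per group.
- Two-sample t test with the variance pooled over the two arms: 24 per group.
- Welch test at n = 25: standard error √(1/25 + 25/25) = 1.020, noncentrality 3.0/1.020 = 2.94, about 25.9 degrees of freedom, power 80.8%. At n = 24 the power is 79.1%, so Welch needs exactly 25.
- Loss allowance: 30 × (1 − 1/6) = 25.

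The plan's 25 per group is thus a two-independent-sample figure.

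**2. What the paired t test would test on the same inputs.**
- Standardised change: |−0.5|/1.0 = 0.5 and 2.5/5.0 = 0.5.
- Noncentrality: 0.5 × √25 = 2.5 on 24 degrees of freedom, power 67.0%; 0.5 × √30 = 2.74 on 29 degrees of freedom, power 75.4%.

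This is power to show change from baseline in one arm, and at 25 it is below the stated 80%. The stated sample size therefore does not come from the paired test.

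**3. Illustration: reading a treatment difference from two separate paired tests.** Suppose two arms have the same true standardised change, so that there is no treatment difference. With power p in each arm, the chance that exactly one is significant is 2p(1 − p).

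| True standardised change (assumed, both arms) | n = 25 | n = 30 |
|---|---|---|
| 0 | 9.5% | 9.5% |
| 0.25 | 35% | 39% |
| 0.36 | 48% | 50% |
| 0.5 | 2 × 0.670 × 0.330 = 44% | 2 × 0.754 × 0.246 = 37% |

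**4. Does a between-group test still have enough patients?** For Welch at n = 30, the standard error is √(26/30) = 0.931, the noncentrality 3.22 and the power 87.7%. With baseline adjustment the SD is multiplied by √(1 − ρ²). The correlation ρ is not in the protocol. Assuming 0.1 to 0.5, the normal-approximation n runs from 22.7 × 0.99, so 23, down to 22.7 × 0.75, so 18 per group. The planned 30 is enough in either case.

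**The case against.** The best defence is that the efficacy sentence is a loose list, not a plan to judge treatment by within-group tests. The Summary plans comparisons between groups, the null is between-group, and section 9.2 itself limits the paired test to changes within a group. A rank test could compare Sharp score change between arms, and chi-square can compare ACR response rates. Details may sit in an analysis plan that is not shown.

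Much of this stands, and it rules out several stronger readings:
- A reader might infer that the plan yields only within-group p-values and no valid test of treatment. The text does not support that, because two of its three options can be between-group.
- A reader might take 44% as the trial's error rate. It is not. The protocol nowhere says that a difference is declared when one arm is significant and another is not. The figure also assumes equal changes, whereas the planning means have opposite signs.
- A reader might infer that one variance would be pooled over all three arms. No such method appears, and no SD is given for Group B.
- A reader might call it an error that centre and baseline Sharp score are not named as covariates, given allocation "using centre-stratified block-permuted randomization, with 30 patients in each group and 90 patients in total". A protocol may leave covariates to the analysis plan. Baseline already enters through the change score, and omitting either does not invalidate a randomised comparison.

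What the defence does not answer is that section 9.2 does name tests, and the parametric one it names for efficacy is by its own definition within-group. An analysis plan that used a two-sample method would have to depart from this sentence.

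**Conclusion.** The point holds in this form. Section 9.2 names a within-group test as the only parametric test of efficacy, leaves the nonparametric alternative unidentified, and so fixes no between-group test for Sharp score change. That conflicts with the objective and with the hypothesis for which 25 per group was calculated.

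The conflict rests on the protocol's own words and on the planning values in section 9.2. The 44% and 37% rest on two further assumptions: equal true standardised changes of 0.5, and an inference practice that the protocol does not describe. They show why separate paired tests cannot stand in for a comparison and are not a forecast for this trial. The sample size is not wrong on this account. Because the primary conclusion depends on this sentence, it should be corrected.

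**What to change.** Replace the efficacy sentence in section 9.2 with wording to this effect:

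- The primary analysis compares the change in Sharp score from baseline to Week 52 between the randomised groups, for a named pair of groups. It uses one pre-named method that allows unequal variances, since the planning SDs are 1.0 and 5.0, and reports the mean difference with its 95% CI. A Welch test and an analysis of covariance with heteroscedasticity-robust standard errors are both reasonable choices.
- ACR response rates are compared between groups by chi-square, or by a version stratified by centre.
- Paired t tests are descriptive within-group summaries and are not used to infer a treatment difference.

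Adjustment for baseline Sharp score and centre is a recommended addition, not the correction of an error. With 90 patients over the seven sites in section 10.1, the average is 90/7 ≈ 13 per site, or about 4 per arm, so very small centres would need a pre-stated pooling rule.

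The cost is wording only. Baseline Sharp score and centre are already recorded, no patients are added, and Welch power at 30 per group is 87.7% on the plan's own assumptions.
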